**Chief investigator**

[name] will act as the Chief Investigator (CI) for the duration of this study. The CI will be responsible for overall study management and maintenance of the site file and all data collected from this study. The CI will be responsible for ensuring that all other investigators have received suitable training according to their role in the study.

**Steering group**

The steering group will be regularly throughout the study to review ongoing recruitment, processes, and consider when study amendments might be necessary.

**Other researchers**

All researchers at participating sites will be required to sign the delegation log, as authorised by the PI.

| **Amendment number** | **Protocol version number** | **Date of amendment** | **Type of amendment** | **Summary of amendment** |
| **1** | **3.0** | **11.09.2025** | **Substantial** | **Addition of second EEG measure at visit 3** |
| **2** | **4.0** | **30/10/2025** | **Minor** | **Addition of Be Part of Research Volunteer network to recruitment strategy** |
| **3** | **5.0** | **27/11/2025** | **Substantial** | **Addition of Qualitative Interviews after visit 3**  **Extension of study date**  **Additional of additional collabortaors** |

Study summary

| **Study Title** | REsilience PROmotion with GeRoprotectors: AssessMent of biological effect (REPROGRAM study) |
| --- | --- |
| **Study Registration** |  |
| **Sponsor** | University of Birmingham  [name]; [[contact]](mailto:[contact]) |
| **Funder** | Wellcome LEAP Dynamic Resilience programme |
| **Study Design** | Open Label, uncontrolled, Non-CTIMP |
| **Study Participants** | Older volunteers – 70 years and older |
| **Planned Recruitment** | 60 participants (20 each agent; 50% female) |
| **Follow Up Duration** | 5 weeks for each participant |
| **Planned Study Period** | June 2024 – December 2026 |
| **Primary Research Question** | Does a three week course of metformin, spermidine, or fisetin reduce the number of senescent cells as measured by SA-β-GAL in adipose biopsies in healthy older volunteers? |
| **Intervention** | Metformin MR – 500mg once a day for one week and then 1500mg once a day for three weeks, oral administration  Fisetin – 100mg once a day for three weeks, oral administration  Spermidine – 15mg once a day for three weeks, oral administration |

Study schema

[figure not shown]

 Day 28/35 Clinical Visit may be + 3 days

Study protocol

**Resilience PROmotion using GeRoprotectors: AssessMent of biological effect (REPROGRAM study)**

1. Background

Doubling of life expectancy in the last 200 years is testament to success of public health and medical advances. However, population ageing presents a major health and social care challenge. As we age, our biological systems and clinical features become increasingly diverse. This diversity can lead to either healthy ageing or development of age-related conditions such as frailty, sarcopenia, and cognitive decline (1). Advancement of age is associated with reduced resilience, hindering the ability to maintain balance and stability when confronted with infections, falls, or surgery (2). This loss of dynamic resilience with age, whilst universally recognised, is poorly defined or understood biologically, limiting our ability to intervene to maintain health in old age.

Advances in ageing biology have enabled the description of key biological mechanisms driving the aged phenotype, the hallmarks of ageing (3), including: reduced mitochondrial fitness, telomere shortening, reduced autophagy, accumulation of senescent cells, microbial dysbiosis and increased systemic inflammation. Importantly, targeting these ageing processes, for example by deleting senescent cells (4), extends healthspan in mice, reducing development of age-related conditions. Geroprotectors are drugs which can affect underlying ageing processes rather than a single symptom or disease. However, there is an absence of robust pharmacodynamic and pharmacokinetic data on their ability to modify the proposed targets in vivo in humans. Additionally, it is unclear which patients should be treated and where in their life-course the drugs will have the optimum effect (5).

This study aims to investigate three different agents, metformin, fisetin and spermidine, and determine their ability to modify biological pathways in vivo in humans. These agents have been chosen as drugs with both evidence of effect on the hallmarks of ageing and good safety profiles in frail, older adults. Metformin, an oral hypoglycaemic agent, has been used safely in frail, older adults for over 60 years (6). Fisetin, a plant flavonol, and spermidine, a natural polyamine, can both be bought as a supplement in the UK and have no reported side effects (7) (8, 9).

Metformin lowers the incidence of multiple age-related diseases, including frailty, as well as all-cause mortality in adults with diabetes (10, 11). In non-diabetic mice and C. elegans metformin extends both lifespan and some indicators of healthspan including muscle strength and gait speed (12) (13). There is evidence in cell lines, drosophila, C. elegans and mice that metformin modulates multiple hallmarks of ageing: nutrient sensing, intracellular communication, proteostasis, genomic instability, mitochondrial function, stem cell exhaustion, epigenetic alterations, telomere attrition and cellular senescence (14). There is some evidence that metformin influences healthspan in non-diabetic adult humans. Laksmi found that metformin improved walk speed in pre-frail adults (15) but the MASTERS trial found no benefit of using metformin as augmentation to resistance training (16). MET-PREVENT (17) and TAME (18) are yet to report on their outcomes of using metformin in older adults with sarcopenia and pre-frailty or frailty and older adults respectively.

Fisetin is found in edible fruits and vegetables such as strawberries, apples and persimmons (19). Fisetin is a senolytic agent and reduces the number of senescent cells in a variety of animal and tissue models (20, 21). Fisetin in mice has been demonstrated to extend both life and healthspan (22). There are several ongoing studies and studys in humans none of which have yet reported (23).

Spermidine is found at high levels in many food products including dry soy beans, chicken liver and blue cheese (24). It is an essential metabolite that exhibits age-dependent decline in a number of models including humans (25). It is believed to effect multiple hallmarks of ageing but the evidence is limited (25). In yeast, C. elgans, mice and rat models spermidine increased lifespan and in rats healthspan (25). Epidemiological studies have demonstrated that diets high in spermidine are associated with lower mortality (26). There are number of ongoing clinical trial investigating spermidine in age related diseases such as hypertension and heart failure (25).

1. Rationale

Patient and public involvement

Patient representatives have been actively involved in the design of this study and will act as members of the steering group throughout the study. Patient representation will be imperative in considering the implications of the study, and will be actively involved in interpretation and dissemination of results.

Rationale for research questions – relevance to NHS patients and healthcare policy

Advancements in medicine have led to increased life expectancy through improved treatment of conditions such as cancer, heart disease, and infections{Loh, 2013 #148}{Statistics, 2017 #149}. However, these improvements in lifespan have not been associated with increases in healthspan (the number of years spent in good health). It is known the outcomes that are important to older people is not always longevity, but rather perceived quality of life. This study aims to determine whether targeted interventions towards underlying biological mechanisms associated with poor resilience can change the biological pathways within a 3 week period. It is undetermined when geroprotectors should be given in an individual’s lifecourse to have the greatest effect but research increasingly supports intervention at an early stage to modify the development of age-related disease and multimorbidity{Lee, 2023 #150}{Kennedy, 2014 #151}. We have previously conducted a study of a multi-component supplement in healthy older adults which demonstrated an improvement in epigenetic age{McGee, 2024 #152}. This is a similar approach to other studys and studies of geroprotector agents: metformin {Walton, 2019 #153} and rapamycin {Chung, 2019 #155}{Kraig, 2018 #156}{Mannick, 2014 #154}

Rationale for study design

This study is a Phase 2a clinical study. It is designed to investigate the effect of the intervention on biological outcomes. The intervention, metformin, spermidine or fisetin, will be administered for three weeks to healthy volunteers. This mimics the time between a diagnosis of localised cancer and curative surgery and will attempt to determine whether these agents could be used effectively in the prehabilitation process to prevent loss of resilience post-surgery. Healthy volunteers are being recruited to the study rather than patients because the biological outcomes of these interventions for this duration are unknown.

1. Research question/aims

Objectives

Primary Research Question

- Does a three week course of metformin, spermidine, or fisetin reduce the number of senescent cells as measured by SA-β-GAL in adipose biopsies in healthy older volunteers?

Secondary Research Questions

- Does a three week course of metformin, spermidine, or fisetin reduce senescence in healthy older volunteers?
- Does a three week course of metformin, spermidine, or fisetin reduce mTOR activation in healthy older volunteers?

Outcomes

Primary Outcome

- Number of senescent cells in adipose tissue measured by SA-β-GAL technique after three weeks of intervention, adjusted for baseline number of senescent cells prior to the intervention.

Secondary Outcomes

- Senescent cell burden in adipose tissue as measured by transcriptomics using SenMayo analysis after three weeks of intervention, adjusted for baseline number of senescent cell burden prior to the intervention.
- Epigenetic age (DNA methylation) after three weeks of intervention, adjusted for baseline epigenetic age prior to the intervention.
- Immunesenescence as measured by IMM-AGE analysis after three weeks of intervention, adjusted for baseline IMM-AGE prior to the intervention.
- Autopahgic flux as measured by flow cytometry after three weeks of intervention, adjusted for autophagic flux prior to the intervention.
- Nutrient sensing as measured by mTOR activation after three weeks of intervention, adjusted for baseline nutrient sensing prior to the intervention.
- Mitochondrial function as measured by Seahorse after three weeks of intervention, adjusted for baseline mitochondrial function prior to the intervention.
- Inflammation as measured by ELISA and multiplex technology after three weeks of intervention, adjusted for baseline inflammation prior to the intervention.
- Microbial composition and functional potential of stool using metagenomics after three weeks of intervention, adjusted for baseline microbial composition and functional potential prior to the intervention.
- Changes in neural oscillatory signatures measured by EEG.

1. Study design and methods of data collection and data analysis

This study is a Phase 2a clinical study. It is designed to investigate the effect of the intervention, metformin, spermidine, or fisetin, on biological outcomes. Additionally, an embedded qualitative interview sub-study will be undertaken with a sub-sample of participants enrolled in the REPROGRAM trial. See section 8 for information about the qualitative sub-study.

Power Calculations

The sample size calculation is based on measurements of SA-β-Gal from a senolytic study in adults (27). The number of participants required at 80% power and a significance level of 0.05 to detect a mean difference of 5% in SA-β-Gal marker is 9. To allow for drop out 10 participants of each sex will be recruited to each intervention (metformin, spermidine, or fisetin), 20 in total. We are recruiting 10 participants of each sex for each intervention as there is some evidence of sex differences with women believed to be more prone to senescence (28).

Data management

Investigator Site Files (ISF) will be maintained for the duration of the study. Source data will be collected on paper CRFs and/or eCRFs on REDCap secure software. Data collected on paper CRFs will be transferred to eCRFs on REDCap. Paper CRFs and consent forms will be held securely at the University Hospitals Birmingham NHS Foundation Trust and will not leave this site. These should be filed within the ISF, or the location of these should be stated clearly if filed elsewhere. Electronic ISFs may be used, but hard copy case report forms and completed paper CRFs must be securely maintained on site. Hospital sites will be responsible for the secure archiving of data. Data will be stored as per the Data Protection Act, 2018.

Data will be securely uploaded through REDCap, which is secure encrypted data management software. Access to REDCap will be provided to users at an appropriate level, with roles setup accordingly. Patient identifiers including date of birth, and participant names will be securely recorded within REDCap for individual participants. Postcodes will be recorded to enable estimation of multiple deprivation indices. Data will be archived for ten years.

Data analysis

Data analysis will be conducted using appropriate statistical software packages by individuals with appropriate expertise. It is envisaged that simple statistical methods (such as t-tests and Mann-Whitney dependent on the normality of the data) will be complemented with more complex analysis using bio-informatic techniques.

Data Protection

All laboratory specimens and CRFs will be identified in a manner designed to maintain participant confidentiality. Laboratory specimens will arrive at the lab in a pseudo-anonymised form. The anonymisation will be done by the person taking the sample. All EEG data will be securely stored in line with institutional data protection policies. EEG recordings do not contain identifiable information and cannot be used to recognise or identify individual participants. The data reflects brainwave patterns only and is stored securely without any personal details attached. All records will be kept in a secure storage area in the Inflammation Research Facility with limited access to study staff only. Information will not be released without the written permission of the participant, except as necessary for monitoring and auditing by the Sponsor, its designee or Regulatory Authorities. The CI and study staff involved with this study will not disclose or use for any purpose other than performance of the study, any data, record, or other unpublished, confidential information disclosed to those individuals for the purpose of the study.

The CI and study staff involved with this study will comply with the requirements of the Data Protection Act 2018 with regard to the collection, storage, processing and disclosure of personal information and will uphold the Act’s core principles. Access to collated participant data will be restricted to the CI and appropriate study staff.

Computers used to collate the data will have limited access measures via user names and passwords.

Published results will not contain any personal data that could allow identification of individual participants.

GP Notification

We will inform the GP of the participants involvement in the study and any clinical information that would be beneficial for the participants’ ongoing healthcare.

Intervention

Participants will be randomly allocated to either Metformin MR, spermidine or fisetin on Day 0 Clinic Vist. Participants will be randomised by the study team using software which will perform stratified randomisation. There will be an equal number of men and women within each drug group and 20 participants within each group.

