Epigenetic age and epigenetic response (at days 0, 30 and 90) will be assessed from isolated whole blood DNA using the Illumina EPIC array and published algorithms **(43)**. Immunesenescence will be assessed by deriving the IMM-AGE score **(36)** by immunostaining and flow cytometry analysis of isolated PBMCs identifying 8 immune cell types (total T cells, naive CD4 T cells, effector memory CD4 and CD8 T cells, EMRA CD8 T cells, CD28− CD8 T cells, CD57+ CD8 T cells and regulatory T cells). Epigenetic age and immunesenescence are associated with risk of morbidity and mortality. Immunesenescence has been shown in mice to be a key driver of frailty **(44)** and in humans to predict impaired resilience in patients following traumatic injury **(45)**. Autophagic flux assessed by LC3-II breakdown by flow cytometry will determine compromised autophagy from whole blood **(46)**. T cells will be assessed for mTOR activation (by phosphoflow cytometry) and mitochondrial function (measuring cellular energetics using a Seahorse system) as further hallmarks of ageing. Stem cell exhaustion, a hallmark of ageing, will be assessed in mesenchymal stem cells (MSCs) isolated from peripheral blood, to evaluate multipotency, senescence and metabolic plasticity.

Adipose tissue to assess cellular senescence and tissue-based resilience biomarkers

Transcriptomics analysis (bulk RNAseq), will allow assessment of senescent cell burden using the SenMayo analysis (47). This will be used to identify associations between dynamic resilience and canonical signalling pathways that mediate muscle mass and myogenesis (Ingenuity Pathway Analysis) and adipogenesis linked with dynamic resilience or progression of frailty. Protein coding and non-coding RNAs associated with resilience will also be assessed. Primary adipose-derived stem cells (ADSC will be isolated from a third of the tissue and assessed immediately for autophagic flux and mitochondrial function or frozen for later use. The remaining snap frozen tissue will be analysed histologically to confirm the presence of senescent cells (Lamin B1, SA-β-Gal, TAF) and lipid accumulation (e.g., Oil Red O staining).

Inflammatory and senescence markers

Analysis of frozen serum using ELISA and multiplex technology will allow assessment of systemic inflammatory and senescence markers.

1. Safety reporting

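### Nothing in the protocol masks the reader of the SA-β-Gal primary endpoint to visit or agent; the only specimen coding described is for confidentiality

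*Protocol*

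**What the plan says.** - **Design.** The study summary gives the design as "Open Label, uncontrolled, Non-CTIMP". Under Intervention, participants are allocated at random to metformin MR, spermidine or fisetin. All three arms are active. On who allocates: "Participants will be randomised by the study team using software which will perform stratified randomisation".
- **Primary outcome.** "Number of senescent cells in adipose tissue measured by SA-β-GAL technique after three weeks of intervention, adjusted for baseline number of senescent cells". The primary research question is directional: it asks whether the count is reduced. Table 2 places the adipose biopsies at the Day 0 visit and at Day 28/35.
- **How it is read.** The laboratory methodology section, under adipose tissue, says: "The remaining snap frozen tissue will be analysed histologically to confirm the presence of senescent cells", and lists SA-β-Gal among the markers. It gives no reader, no counting rule, no automated scoring and no masking.
- **Specimen coding.** The Data Protection text opens with its purpose: "All laboratory specimens and CRFs will be identified in a manner designed to maintain participant confidentiality". It continues: "Laboratory specimens will arrive at the lab in a pseudo-anonymised form. The anonymisation will be done by the person taking the sample".

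In the text at hand, the word blind occurs only in the titles of cited studies.

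**The concern.** Open-label dosing does not require open reading of slides. For a laboratory endpoint, masked reading is the safeguard still available when participants and clinicians know the treatment, and the protocol does not provide for it.

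Pseudonymisation and masking do different jobs. A pseudonym hides who the participant is. In a before-after question, what needs hiding is whether a slide comes from before or after treatment and, for any comparison between agents, which agent was taken. The code is applied by the person taking the sample, who knows which visit it is, and nothing says the code conceals that from the reader.

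The lack of an untreated arm sharpens this. With such an arm, a shift tied only to the visit would affect both groups and largely cancel in the comparison. Here it is added to every participant's change and has the same form as the effect being sought. If the reader also knows the agent, the shift could differ between arms.

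**Working it through.** **What the sample-size text allows.** Under Power Calculations the protocol states that 9 participants are needed for 80% power at a significance level of 0.05 to detect a mean difference of 5% in SA-β-Gal. It gives no SD, test or sidedness, so the 9 cannot be reproduced forwards. It can be solved backwards for the SD of the within-person change, reading 5% as 5 percentage points.

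- Two-sided paired t-test, n = 9, 8 df, critical value 2.306. Power of 0.80 needs a standardised change d = 1.067, so SD = 5 / 1.067 = 4.69.
- The same test reaches 80% power at n = 8 with d = 1.156, so SD = 5 / 1.156 = 4.33. An SD above 4.33 and up to 4.69 therefore rounds up to n = 9.
- Normal approximation, two-sided, n = 9: SD = 5 × 3 / (1.960 + 0.842) = 5.35.
- Normal approximation, one-sided, n = 9: SD = 5 × 3 / (1.645 + 0.842) = 6.03.

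The range carried forward is 4.33 to 6.03 points.

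**Completers.** The protocol recruits 10 of each sex per agent to allow for drop-out from 9, which gives 2 × 9 = 18 completers per agent.

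**Effect of a reading shift.** Let the true change be zero and let follow-up slides be read systematically b points differently from baseline slides. The two-sided paired t-test then rejects with the probability that a noncentral t variable with 17 df and noncentrality b × √18 / SD lies outside ±2.110. For b = 1 and SD = 4.69, the noncentrality is 1 × 4.243 / 4.69 = 0.905 and the rejection probability is 13.7%.

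| Reading shift b | Share of the 5-point target | SD 4.33 | SD 4.69 | SD 5.35 | SD 6.03 |
|---|---|---|---|---|---|
| 0 | 0% | 5.0% | 5.0% | 5.0% | 5.0% |
| 0.5 point | 10% | 7.5% | 7.1% | 6.6% | 6.3% |
| 1 point | 20% | 15.2% | 13.7% | 11.6% | 10.2% |
| 2 points | 40% | 45.6% | 40.0% | 32.2% | 26.4% |

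If all 20 per agent complete, a 2-point shift gives 29% to 50%. In an analysis of 10 of one sex it gives 16% to 26%. Masking changes no sample size: it is meant to bring b to zero and so return the error rate to 5%.

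**The case against.** The strongest reply is that this is silence and not error. The quoted sentence is a correct confidentiality statement and does not claim to describe blinding. Slide coding and reading order may sit in a laboratory manual that is not shown. That is fair as far as it goes. But how specimens are coded is a matter of conduct that has to be settled before slides are read. The protocol does describe a coding, and the coding it describes serves another purpose.

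Several stronger readings are tempting, and the documents do not support them:

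- *That the count is made by eye.* The text says only that tissue is analysed histologically. Software scoring is possible, though someone would still have to set it up.
- *That the label shows participant and visit.* The protocol says only that specimens are pseudo-anonymised. A code unique to each specimen would also fit and could hide the visit.
- *That the person taking the sample knows the agent at both biopsies.* Randomisation, biopsy and drug supply all fall on Day 0 and their order is not stated, so at baseline the agent may be unknown.
- *That the damage could never be repaired.* Adipose samples are stored at -80°C for ten years, so a masked re-read may be possible where tissue remains. The SenMayo transcriptomic outcome gives a second view of adipose senescence that needs no slide reader.
- *That the flow cytometry outcomes share the problem.* The protocol does not describe how those data are gated, so nothing can be said either way.

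The arithmetic is also open to the reply that the shifts have no source. That stands: the table shows what a shift would do, not how likely one is.

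**Conclusion.** The point holds in a limited form. The protocol leaves the reader of the primary endpoint free to know visit and agent, in an open-label design with no untreated arm that could cancel a visit-related shift. A shift of 0.5, 1 or 2 points would raise the false-positive rate from 5% to about 6–8%, 10–15% or 26–46% with 18 completers per agent.

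Those figures assume that 5% means percentage points, that the test is a two-sided paired t-test, that the SD of change lies between 4.33 and 6.03, and that there is no true effect. A reader might infer that the trial's SA-β-Gal result will be biased. The documents do not show that; they show that nothing stated prevents it. Because the safeguard is cheap and protects the primary endpoint, the sponsor should add it.

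**What to change.** Add to the Data Protection text, and repeat in the adipose tissue paragraph of the laboratory methodology section, that:

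1. each adipose biopsy receives a random laboratory code that carries neither participant number, visit nor agent, assigned by an existing team member who does not read the slides;
2. a participant's two biopsies are read in random order by a reader masked to visit and agent, or scored by software whose settings are fixed while masked;
3. SA-β-Gal counts are locked before the code is broken.

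The cost is a relabelling step, a code list to keep, and a wait to read baseline slides until the follow-up biopsy is available. The protocol already freezes the tissue used for histology. Sample size, visits and procedures for participants do not change.
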